#### Qualitative data collection

Additionally, 2 focus groups will take place with patients and 2 focus groups will be developed with family carers. Another focus group with professionals delivering the intervention will be held.

The selection of patients and family carers will be made by means of intentional sampling with maximal variety [35], to promote the selection of participants from the intervention group of different ages, gender and number of years experience living with PD. These focus groups will take place 6 months after the ReNACE psychoeducational intervention was delivered. The aim of these focus groups is to explore the patients’ and family carers’ perceptions of the benefits of the ReNACE intervention in terms of coping skills, psychosocial adjustment and quality of life. Furthermore, participants will be asked their opinion on the issues covered and the methodology used. These focus groups will not be used to compare satisfaction with the interventions between groups (control versus experimental) because their goal is to understand better the changes related to the ways of coping of participants, that will be worked only in the ReNACE psychoeducational intervention. To this end a semi-structured interview guide will be used with questions such as the following displayed in Table 5.

**Table 5 Tab5:** Questions to guide the focus groups of participants and healthcare professionals

Focus groups with people with Parkinson and family carers
• What do you think of the contents of the workshop?
• What do you think about the way in which the workshop took place?
• Could some aspects be improved?
• What have you got from participating in these workshops?
• How would you now rate your ability to cope with the disease?
Focus group with healthcare professionals
• What is your opinion of the content of the intervention?
• What do you think about the way in which the intervention took place?
• How do you think the information has been understood by the participants?
• What was the attitude of the participants in the intervention?
• How do you think the intervention may have influenced the psychosocial adjustment of the patients and family members?
• How might the sessions have changed the attitude of the participants to cope with the disease?
• How do you think could be the implementation of the intervention into care pathways?

The focus group with the social and healthcare professionals responsible for imparting the ReNACE psychoeducational intervention will be organised once the intervention has finished. The aim of this analysis is explore the professionals’ perspectives of the intervention and its integration as part of care pathways, their role in its future implementation, time needed and costs. A semi-structured interview guide will be used to guide the dialog around the questions shown in Table 5.

In all the focus groups voice recordings will be made which will subsequently be transcribed.

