To favor the collection of data at the most appropriate moment, participants will be given an appointment in their local centre to answer the questionnaires at T0 and T1. If participants do not attend these meetings they will be contacted by telephone to explain that the questionnaire will be sent by postal mail and that they should hand it in the centre or send it in the stamp addressed envelope within the period of 1 week. Furthermore, they will be given a telephone number that they can ring should they have any doubts about the questionnaire. For the evaluation of the results at T2 (6 months post-intervention) the questionnaires will be sent by post to all the participants and the same process as described above will be followed for their collection.

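### Focus groups on perceived benefit are held only in the intervention arm at the same nominal 6 months as T2, and nothing requires T2 to be returned first

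*Protocol article*

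**What the plan says.** All references are to the protocol article.

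- **Who attends.** Qualitative data collection plans that "2 focus groups will take place with patients and 2 focus groups will be developed with family carers". Sampling is purposive and limited to one arm: "to promote the selection of participants from the intervention group of different ages, gender and number of years experience living with PD". No control-arm counterpart is planned, and the section gives a reason: the ways of coping under study are worked on only in ReNACE.
- **When.** "These focus groups will take place 6 months after the ReNACE psychoeducational intervention was delivered".
- **What is discussed.** The aim is to explore "perceptions of the benefits of the ReNACE intervention in terms of coping skills, psychosocial adjustment and quality of life". Table 5 includes the prompt "How would you now rate your ability to cope with the disease", and also asks what members took from the workshops and what could be improved.
- **T2.** Quantitative data collection states: "For the evaluation of the results at T2 (6 months post-intervention) the questionnaires will be sent by post to all the participants". The instruments are PDQ-39 or SQLC, PAIS-SR and Brief COPE, all completed by the participant.
- **Calendar.** Table 1 marks patient and carer focus groups in Q5, Q6 and Q7, and T2 collection in Q3, Q5, Q7, Q9 and Q11.
- **Use of T2.** Under Data analysis, T2 has its own between-group t test and is one of the three time levels in the mixed factorial ANOVA.

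The article gives no order between a member's focus group and that member's T2 questionnaire.

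**The concern.** A member who attends the group first has spent a session with peers and a facilitator talking about what ReNACE did for coping, adjustment and quality of life. That member then rates the same constructs at home. No control participant has such a contact. Any effect on the answers would enter the T2 between-arm difference and could not be separated from a lasting effect of the programme.

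T2 is the only measurement that speaks to durability. The Discussion notes that most earlier studies found no significant long-term result or did not evaluate one, so a T2 difference here would carry weight. T0 and T1 come before the groups, so a disturbance confined to T2 could be read as benefit sustained or lost.

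**Working it through.** **1. Is an order fixed?**

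| Table 1 period | T2 collection | Patient/carer focus groups |
|---|---|---|
| Q3 | yes | no |
| Q5 | yes | yes |
| Q6 | no | yes |
| Q7 | yes | yes |
| Q9 | yes | no |
| Q11 | yes | no |

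Table 1 has 12 columns for four years, so each spans about four months. Sharing a column shows only that the two activities may be close in time; it does not give their sequence. The text gives the same 6 months for both and no sequence either. Both orders comply with the plan.

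**2. Expected completers (Table 2).** The plan's sizes reproduce first. Table 2 gives no alpha; 0.05 two-sided is assumed.

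- Patients: n = 2(1.96 + 0.84)² × 15.44² / 10² gives 38 per group, or 39 with the t distribution; 39 / 0.75 = 52, as stated.
- Carers: the same formula with SD 25.04 and difference 15 gives 44; 44 × 1.20 = 52.8, or 53 as stated (dividing by 0.80 would give 55).

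Expected completers per arm are 52 × 0.75 = 39 patients and 53 × 0.80 = 42.4 carers. The point does not depend on how the losses were applied.

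**3. Share of the arm exposed.** Group size is not stated; 6 to 10 is assumed. Two groups then hold 12 to 20 people.

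- Patients: 12/39 = 31% to 20/39 = 51%.
- Carers: 12/42.4 = 28% to 20/42.4 = 47%.

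**4. Movement of the arm mean at T2.** Bias = f × (members / completers) × shift per member, where f is the fraction of members who answer T2 after their group. The table sets f = 1. The shifts are assumptions, set at 10%, 25% and 50% of the Table 2 difference.

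| | Shift per member | Arm mean moves (12 to 20 members) | Share of planned difference | Two-sided type I error |
|---|---|---|---|---|
| Patients | 1 | 0.31 to 0.51 | 3% to 5% | 5.1% to 5.2% |
| Patients | 2.5 | 0.77 to 1.28 | 8% to 13% | 5.6% to 6.6% |
| Patients | 5 | 1.54 to 2.56 | 15% to 26% | 7.2% to 11.4% |
| Carers | 1.5 | 0.42 to 0.71 | 3% to 5% | 5.1% to 5.2% |
| Carers | 3.75 | 1.06 to 1.77 | 7% to 12% | 5.4% to 6.2% |
| Carers | 7.5 | 2.12 to 3.54 | 14% to 24% | 6.8% to 10.0% |

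Type I error is Φ(−1.96 + c) + Φ(−1.96 − c), with c = bias / SE and SE = SD√(2/n). This is a simple two-sample comparison of individuals at T2. For the largest patient case, SE = 15.44 × √(2/39) = 3.50 and c = 2.56/3.50 = 0.733, so Φ(−1.227) + Φ(−2.693) = 0.110 + 0.004 = 11.4%.

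**5. The other order.** With f = 0 every entry for movement of the mean is 0 and the type I error is 5%.

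**The case against.** The strongest reply is that the harmful order is nowhere written. A reader might infer that ReNACE participants attend a focus group just before they fill in T2, and that the result is biased in favour of ReNACE. The documents support neither step. They give a shared nominal time point, not a sequence. Table 1 also has groups in Q6, when no T2 is collected, and three of the five T2 periods have no focus group. On direction, the guide also invites criticism of the programme, and talking with peers about a progressive disease could move self-ratings either way or not at all. This part of the objection stands.

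It is also fair that a condensed article may leave the order of invitations to a fuller document, that only members of four groups could be affected, and that sampling one arm is a reasoned choice. These points limit the reach of the problem. They do not remove it, because the article itself fixes the arm, the time point, the aim and the questions, and that combination leaves T2 unprotected.

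Last, on the Table 1 calendar the groups fall in 2016 to early 2017, so changing the order may come too late for most of them. That also stands, and the fix therefore covers groups already held.

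**Conclusion.** The point holds as a limited one. The plan permits a contact in one arm only, about the outcome constructs, before T2 for members of the four groups. It does not require such a contact or document that it happens.

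Given 6 to 10 people per group and a shift of 1 to 5 PDQ-39 points each, the patient arm mean among 39 completers moves by 0.3 to 2.6 points if every member answers T2 after the group. For those inputs this is an upper bound: it falls in proportion as more members return T2 first, and reaches zero if all do. The 2.6 figure, about a quarter of the 10-point difference, needs the largest group, the largest shift and the unfavourable order for every member, so it should not be quoted as an expected bias. Group size and shift are assumptions, and the sign is unknown.

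**What to change.** **For groups still to be held:** state under Qualitative data collection that a participant joins a focus group only after their T2 questionnaire has been returned.

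**For groups already held:** compare each member's T2 return date with the focus group date, flag those who answered T2 afterwards, and repeat the T2 comparison without them. Report this as a sensitivity analysis beside the intention-to-treat result. Table 1 schedules the quantitative analysis for Q11 and Q12, after the groups, so the flag can be set before the analysis.

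The sensitivity analysis is imperfect. Attendees were purposively selected and come from one arm only, so removing them also changes who is compared. A change in the estimate cannot be attributed to the focus group alone, and the report should say so.

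**Cost:** one sentence, a delay of a few weeks for any remaining focus groups, and one extra analysis.

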### Data analysis

#### Quantitative data

Analysis of quantitative data will be performed on an intention to treat basis and for that SPSS version 23.0 will be used. A descriptive analysis of the sociodemographic data will be made. For the quantitative variables, means and standard deviations will be calculated. Mixed ANOVA within-pairs and between-pairs to compare patients with family carers at each measurement points, unpaired student t tests to determine any significant differences between the two groups at baseline (T0) and the measurements at T1 and T2 will be used. Also, a mixed factorial ANOVA with 1 between-subjects factor with 2 levels (intervention and control), and 1 within-subjects factor with 3 levels (baseline, time 1 post-intervention, time 2 post-intervention) will be used to compare differences between the two groups in the main variables over time. If any demographic variable result different will be use as a covariate in this analysis.

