### Setting

The study will be carried out in several urban areas of Navarra, in the North of Spain. Specifically, the six health centres in a community setting with the largest numbers of people diagnosed with PD will be chosen in order to maximise the recruitment of participants and improve the power of the study. At the end of the recruitment of participants, ANOVA and χ^2^ tests will be performed to explore the sociodemographic characteristics of the participants from the intervention group and the control group. In the case of finding a significant difference in a sociodemographic variable, the statistics analyses will adjust by propensity-score analysis or the most suitable statistical technique.

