The main focus of the intervention is on empowering participants’ coping skills with stressful situations, which could clearly cause a crisis in the positive living with a LTC like PD [21]. This approach seeks that the participants become aware of their cognitive and behavioural efforts, think about them, and choose those that help them better adjust to PD [14]. In particular, professionals will work with the meaning of coping with PD explained by Navarta-Sánchez et al. [14]. All sessions will take place on the same day with the people with PD and their family carers, but in separate groups (see Table 3). This has been planned so as to prevent patients from not expressing themselves freely for fear of hurting the feelings of their family carers and vice versa. At the same time, as is shown in Table 3, the intervention will be delivered by a multidisciplinary team with years of clinical experience working with people with PD and other LTCs. All professionals of this team will use a manual which contains a description of the content and methodology of each session in order to improve adherence to intervention’s characteristics.

Furthermore, in one of the sessions a person with PD and a long history of the disease and a great interest in helping other people with PD to better cope with their situation will participate. Precisely with this objective, this person wrote a book, which will be offered for free as supportive written material to the participants. Also, in all the sessions participants will receive a document summarising the content covered and presented during the session on a projection screen.

The attendance of participants will be controlled in all sessions so that these data are available for analysis of the results. Those participants not attending at least 70% of the intervention sessions will be counted as lost to the study. Bearing in mind the complexity of the recruitment process and the duration of the interventions, it is expected that the interventions will need to be delivered over a period of 18 months.

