### Outcome measures

#### Quantitative data collection

The primary outcome is the improvement in quality of life of the people with PD and of the family carers participating in the ReNACE psychoeducational intervention, in comparison with the change observed in the quality of life of those participating in the general educational programme. The secondary outcomes will be the changes in the coping skills and in the psychosocial adjustment to PD. These outcomes will be measured in the control and intervention groups at 3 time points; baseline (T0); immediately after the end of the intervention (T1); and 6 months post-intervention (T2). To ensure blinding of the groups and the intervention, researchers involved in data collection will not have participated in any of the group sessions and known the group allocation. At baseline (T0) the sociodemographic data of the participants will be collected. At the three time points the following instruments will be used to measure the outcomes:

Patients:The Quality of Life Scale in Parkinson’s disease (PDQ-39) [29, 30]The Psychosocial Adjustment to Illness scale (PAIS-SR) [31]The Brief COPE scale [32, 33]

Family carers:The Scale of Quality of Life of Care-givers (SQLC) [23, 34]The Psychosocial Adjustment to Illness scale (PAIS-SR) [31]The Brief COPE scale [32, 33]

The measurement scales selected are validated instruments which furthermore, have been used previously in a study of the ReNACE programme in PD patients and their family carers [11].

It is calculated that the participants will need approximately 1 hour to complete the questionnaires. When the participants finish the questionnaire, the researcher will check that they have been filled in correctly in order to minimise data loss.

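### Neither planned comparison of quality of life adjusts for the baseline score, although the primary outcome is change relative to control; a baseline-adjusted mixed model should be the primary analysis

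*Protocol article*

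**What the plan says.** Under Outcome measures, the article defines the primary outcome as the improvement in quality of life in the ReNACE group, "in comparison with the change observed in the quality of life of those participating in the general educational programme". The outcome is therefore a difference in change.

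Under Data analysis (Quantitative data), two analyses bear on it:

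- "unpaired student t tests to determine any significant differences between the two groups at baseline (T0) and the measurements at T1 and T2". The T1 and T2 tests use the score at that visit alone.
- A mixed factorial ANOVA with group as the between-subjects factor and "1 within-subjects factor with 3 levels (baseline, time 1 post-intervention, time 2 post-intervention) will be used to compare differences between the two groups". T0 enters as an outcome level, not as a covariate.

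Neither analysis is named as primary. The only covariate rule for the ANOVA is "If any demographic variable result different will be use as a covariate in this analysis". The Setting section adds: "In the case of finding a significant difference in a sociodemographic variable, the statistics analyses will adjust by propensity-score analysis", or another suitable technique. Both rules are triggered by demographic differences, and neither names the baseline quality-of-life score.

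The same paragraph states: "Analysis of quantitative data will be performed on an intention to treat basis". Table 2 expects losses of 25% for patients and 20% for carers. The T2 questionnaire goes out by post. The section on the intervention adds: "Those participants not attending at least 70% of the intervention sessions will be counted as lost to the study".

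**The concern.** The T1 and T2 t tests do not estimate the stated outcome. They compare levels, so any difference between the arms at T0 passes partly into the result. The design makes such a difference plausible: whole centres were allocated by coin toss, there are only six, and the Limitations section itself lists baseline differences between centres. Its answer is that significant differences between participants are not expected, which does not protect a raw comparison.

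The ANOVA does use T0, but not efficiently. It tests a 2-degree-of-freedom interaction where a direct contrast would do, and it treats T0 as an outcome rather than as a predictor of later scores. In its conventional form it also needs all three scores from each participant. With a postal T2 and losses of 20 to 25%, some people will have T0 and T1 but no T2. Dropping them fits poorly with an intention-to-treat label.

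At stake are a shift in the estimated effect, power that the T0 data would supply free of charge, and a primary result that depends on which of several tests is read.

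**Working it through.** **Inputs.** From Table 2: patients SD 15.44, difference 10, power 80%, losses 25%, 52 per group; carers SD 25.04, difference 15, power 80%, losses 20%, 53 per group. Six centres, taken here as three per arm. Assumed because the article does not give them: two-sided alpha 0.05; r = 0.5, 0.6 or 0.7; intraclass correlation (ICC) 0 or 0.05.

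**1. Reproducing the plan's sample size.** For two independent means, n = 2 × (SD × (1.96 + 0.84)/difference)².

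- Patients: 37.4, so 38, and 38/0.75 gives 51. The t-based version gives 39, and 39/0.75 = 52, as stated.
- Carers: 43.7, so 44. 44/0.80 = 55, and 44 × 1.20 = 52.8, so 53, as stated.

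The trial was therefore sized on a single-score comparison with no baseline term.

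**2. Size of a chance baseline difference between arms.** SE = SD × √(2/n × DE), with DE = 1 + (n/3 - 1) × ICC.

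- Patients: ICC 0 gives 15.44 × √(2/52) = 3.03. ICC 0.05 gives DE = 1.82 and SE = 4.08.
- Carers: ICC 0 gives 25.04 × √(2/53) = 4.86. ICC 0.05 gives DE = 1.83 and SE = 6.59.

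**3. What each analysis does with a baseline difference b.**

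- Raw t test at T1 or T2: error r × b. At r = 0.6, patients 0.6 × 3.03 = 1.8 to 0.6 × 4.08 = 2.4 points (target 10). Carers 0.6 × 4.86 = 2.9 to 0.6 × 6.59 = 4.0 points (target 15).
- Group by time interaction, which contrasts change: b is subtracted in full, leaving regression to the mean of opposite sign, (r - 1) × b. At r = 0.6, patients -1.2 to -1.6 points.
- ANOVA group main effect: it averages over T0, T1 and T2, so it does carry the imbalance.

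**4. Variance.** Baseline-adjusted relative to raw = 1 - r² = 0.75, 0.64, 0.51 for r = 0.5, 0.6, 0.7. The raw test thus has 1.33, 1.56 or 1.96 times the adjusted variance.

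**5. Power at the planned completers**, 52 × 0.75 = 39 patients and 53 × 0.80 = 42.4 carers per arm, ignoring clustering. Equal SDs, equal correlations and the same effect at T1 and T2 are assumed. For the interaction, the noncentrality is λ = (n/2) × (2/3 × difference²)/(SD² × (1 - r)) on 2 and 4(n - 1) degrees of freedom. For patients at r = 0.5 this is 19.5 × 66.67/119.2 = 10.9. The baseline-adjusted figure uses SD × √(1 - r²) at one follow-up visit.

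| Power (%) | r = 0.5 | r = 0.6 | r = 0.7 |
|---|---|---|---|
| Patients: raw t test | 80.6 | 80.6 | 80.6 |
| Patients: interaction F | 84.2 | 91.6 | 97.3 |
| Patients: baseline-adjusted | 90.3 | 94.2 | 97.7 |
| Carers: raw t test | 77.8 | 77.8 | 77.8 |
| Carers: interaction F | 81.4 | 89.5 | 96.3 |
| Carers: baseline-adjusted | 88.2 | 92.6 | 96.8 |

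Against the raw t test, adjustment gains roughly 10 to 19 points. Against the interaction it gains 6 to 7 points at r = 0.5, about 3 at r = 0.6, and practically nothing at r = 0.7.

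**The case against.** The strongest reply is that the ANOVA, not the t tests, answers the primary question. It is the analysis assigned to differences between groups over time, and the t tests may be only visit-by-visit description. A reader might infer that the primary result rests on raw t tests and that baseline imbalance contaminates the whole analysis. The article supports neither. It names no primary test, and the interaction removes a baseline difference apart from regression to the mean. This part of the objection stands and limits the point.

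A reader might also infer that a complete-case analysis is prescribed. It is not. The article gives no missing-data rule, and one may exist in a fuller document. What can be said is that the named method, in its usual form, needs all three scores. The number with T1 but no T2 is not given, so the data loss cannot be sized. Anyone lost before T1 gains nothing from the proposed model either.

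A third reply is that, under random allocation, chance imbalance is already in the standard error, so imbalance and lost precision are one problem counted twice. That is largely right for independent participants. It is weaker here, because centres were allocated and an unpaired t test's standard error ignores centre. The rise from 3.0 to 4.1 points in step 2 is not reflected in it.

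Finally, the patient sample is not underpowered for the planned t test: Table 2 was built on that test, and the 80% is reproduced.

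**Conclusion.** The point holds in a limited form. Both planned analyses leave the T0 quality-of-life score out as a covariate, and the T1 and T2 t tests do not match an outcome defined as change. For the t tests the cost is a shift of about 1.8 to 2.4 PDQ-39 points per one-standard-error baseline difference (r = 0.6, ICC 0 to 0.05) and 1.33 to 1.96 times the necessary variance. For the ANOVA interaction the cost is a modest loss of power that vanishes by r = 0.7, plus the probable exclusion of participants with incomplete scores.

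These sizes depend on r, which the article does not give, and on an assumed ICC. The power figures ignore clustering, so they show the relative merit of the analyses and not the power this trial will have. Baseline adjustment also does not remove all bias from voluntary, centre-based participation. The change is worth making because it improves a stated analysis using data already collected.

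**What to change.** For patients and carers separately, name as the primary analysis a linear mixed model fitted by REML:

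- outcomes: the T1 and T2 quality-of-life scores;
- fixed effects: arm, time, arm by time, and the T0 score;
- random effects: participant and centre, with Satterthwaite or Kenward-Roger degrees of freedom because there are only six centres;
- participants: everyone with at least one post-baseline score.

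Report the adjusted arm difference at T1 and at T2 with 95% confidence intervals. Drop the T1 and T2 t tests as outcome tests, and keep the mixed ANOVA as a sensitivity analysis. State that the gain depends on r, and that adjustment does not cure selection into the study.

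The cost is a rewritten analysis paragraph. T0 is already collected in both groups, and Table 1 schedules the quantitative analysis for the last two periods of the project.
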